#### Plans to promote participant retention and complete follow-up {18b}

Measures to help participants cling to the established schedule include:
Seven days prior to their scheduled appointments, participants will receive a reminder message or email where they are notified of the accurate time, place, and recommended preparations for each procedure performed in that duration and they are asked to confirm their attendance. Those who do not reply to the message will receive a phone call.If participants report difficulties in arriving for follow-ups, shortage of time, or inconvenient traffic for example, we will try our best to give assistance, such as adjusting their schedule as long as the time window for each follow-up is not exceeded.We will contact participants who forget to return their questionnaires or miss other examinations within a week to see if they need reminders or other forms of help in the future.

If for any reason they opt to withdraw, no more intervention will be conducted, and no more data will be collected. Data collected before their dropout is used for further analysis under their consent. They will be invited to complete a questionnaire on the reasons for quitting.

#### Plans for collection, laboratory evaluation, and storage of biological specimens for genetic or molecular analysis in this trial/future use {33}

Not applicable as no biological specimens are collected.

#### Plans to give access to the full protocol, participant-level data, and statistical code {31c}

Access to the full protocol, participant-level data, and statistical code will be given by the corresponding author upon reasonable request.

### Data management {19}

Upon enrolment, each participant will be assigned a unique study ID for substitute of their identity information, the only form of participant referral that will be presented on case report forms, used for statistical analysis, and provided for publication.

We will hire a Clinical Research Coordinator and Clinical Research Associate to help with data management. They are obliged to sign a confidentiality agreement before stepping in. Under the supervision of the principal investigator, they fill the case record forms and upload data onto the Epidata. Data are kept in a secure storage that only authorized staff are granted access by the principal investigator.

### Confidentiality {27}

Name and the phone number of potential participants are registered during the routine postpartum consultation if they express interest after reading the recruitment advertisement. Contact information is accessed for the PROSPECT study only by the principal investigator. Upon enrolment, more detailed identity information will be asked merely for legality reviews by national regulatory authorities and Beijing Hospital Ethics Committee and other involved clinical institutions. All personal information mentioned above will be kept in rigorous confidentiality in conformity to laws and regulations. Documentation of this personal information will be permanently locked after the trial.

### Statistical methods

#### Statistical methods for primary and secondary outcomes {20a}

All statistical analyses will be carried out according to the Statistical Analysis Plan and Health Economic Analysis Plan. The primary analysis will be performed at the time right after intervention and at the end of the trial when a 36-month follow-up has been completed. The independent data monitoring and ethics committee (DMEC) will review confidential interim analyses of accumulating data at its discretion, at least annually. The primary effectiveness analysis will be based on the intention-to-treat (ITT) principle.

In the analysis of the primary outcome, we will use the chi-square test to compare the proportion of participants showing improvement of at least 1 level of POP-Q staging among experimental and control groups right after intervention. Furthermore, a binary logistic regression model will be adopted to adjust potential covariate variables like the newborn weight, the length of first/second stage, infant head circumference and the maternal body mass index, etc. For analysis of secondary outcomes, we used appropriate models: the multilevel mixed models for continuous outcomes (PFDI-20, PFIQ-7, PISQ-12, and ICIQ SF-7 scale scores, pelvic floor muscle electromyography values, VAS and QALY of each incremental cost) for the repeated measurements at 6, 12, 24, and 36 months, chi-square test and logistic regression for categorical outcomes (POP-Q staging, pelvic floor muscle strength). The safety index (AE incidence) was analyzed with the chi-square test.

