**Methods:**

This multicenter randomized controlled trial compares the effectiveness and cost-effectiveness of conventional PFMT versus biofeedback-mediated PFMT plus neuromuscular electrical stimulation (NMES) for postpartum symptomatic POP women. The primary outcome is the proportion of patients with the improvement of at least one POP-Q stage at 36 months after randomization. The primary economic outcome measure is incremental cost per quality-adjusted life year at 36 months. Two hundred seventy-four women from four outpatient medical centers are randomized and followed up with pelvic floor examination, questionnaires, and pelvic ultrasonography imaging. All participants are arranged for three appointments over 12 weeks. NMES and electromyography biofeedback via intravaginal probe are added to PFMT for participants in the biofeedback-mediated PFMT group. Group allocation could not be blinded from participants and healthcare staff that deliver intervention but remain masked from medical staff that carry out PFM assessment. An intention-to-treat analysis of the primary outcome will estimate the difference of the proportion of POP-Q stage improvement between the trial groups right after the intervention, and during the follow-up until 36 months, using the chi-square test and multilevel mixed models respectively. A logistic regression analysis was used for adjusting for important baseline variables that are unbalanced.

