#### Primary outcomes

The primary outcome measure is:
The proportion of participants with the improvement of at least one POP-Q stage compared to the baseline data

The primary outcome measure is calculated with each follow-up (M0PI, M6PI, M12PI, M24PI, M36PI, M stands for month, PI stands for post-intervention).

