### Sample size {14}

Previous research has reported that 43.68~62.8% [31–33] of participants in the electrical stimulation plus PFMT group showed improvement in POP-Q staging while 15.4~20.9% [31–34] showed improvement in the PFMT group. Based on early-stage data from the ongoing pilot study, we estimate the proportion of participants with improved POP-Q stage to be 50% in the experimental group and 20% in the control group. Participants are randomized at a 1:1 ratio to the intervention and control groups. We applied a 2-sample superiority test on the proportions to calculate the sample size by PASS software. Based on our clinical treatment experience, we set the testing margin as 15% which indicates the significant clinical effectiveness. Assuming an attrition rate of 20% by the 36-month follow-up, a sample size of 284 women (142 in each arm) is required in the study to provide more than 80% power at a one-sided significance level of 0.05 for the 2-sample superiority test.

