#### Interim analyses {21b}

A single primary analysis will be performed. No interim analysis is planned in the current study.

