#### Methods for additional analyses (e.g., subgroup analyses) {20b}

Subgroup analyses will be performed within the following groups: age (< 35/≥35 years) and additional moderate-intensity exercise (Y/N). The statistical significance level will be set at 5%. Heterogeneity of treatment effects among subgroups will be tested by interactive subgroup analysis.

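### The protocol article disagrees with itself on the primary analysis: 36 months only, both end of treatment and 36 months, or a single analysis; the sample size pays for one test

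*Protocol article*

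**What the plan says.** Four places in the protocol article describe the primary outcome or its analysis, and a fifth sets the error rate.

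- **Abstract, Methods:** "The primary outcome is the proportion of patients with the improvement of at least one POP-Q stage at 36 months after randomization". The same paragraph then describes a chi-square comparison at the end of the intervention and mixed models over the follow-up to 36 months.
- **Primary outcomes (under Outcomes {12}):** "The primary outcome measure is calculated with each follow-up (M0PI, M6PI, M12PI, M24PI, M36PI"; no visit is singled out.
- **Statistical methods {20a}:** "The primary analysis will be performed at the time right after intervention and at the end of the trial", the end of the trial being the completed 36-month follow-up. The only test this section names for the primary outcome, the chi-square, is tied to the first of the two times.
- **Interim analyses {21b}:** "A single primary analysis will be performed".
- **Sample size {14}:** 142 women per arm, "to provide more than 80% power" "at a one-sided significance level of 0.05 for the 2-sample superiority test", with 20% attrition by the 36-month follow-up.

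**The concern.** The Abstract, {20a} and {21b} cannot all be followed. The Abstract and {21b} allow one primary analysis at 36 months; {20a} adds a second one about three years earlier and specifies that one better. The visible text does not say whether 36 months decides, whether both analyses must succeed, or whether either is enough.

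Two things are at stake. First, an end-of-treatment result could be reported as the trial's primary success when the outcome is defined, and attrition budgeted, at 36 months. The Abstract's Background gives unknown long-term efficacy as the reason for the trial, so a short-term gain that later faded could sit beside a claimed positive primary result. Second, if either analysis may win at the level sized for one, the false-positive chance exceeds that level.

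**Working it through.** **Inputs.** From Sample size {14}: 50% improved in the experimental arm, 20% in the control arm, margin 15 percentage points, one-sided 0.05, power 80%, 1:1 allocation, attrition 20%. From {20a}: two primary analysis times. The correlation between the test statistics at the two times is not in the article and is assumed.

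**1. The plan's own figure.** Unpooled normal approximation for a difference in proportions against a margin:

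n per arm = [p1(1−p1) + p2(1−p2)] × (z0.95 + z0.80)² / (p1 − p2 − margin)²

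= (0.25 + 0.16) × (1.645 + 0.842)² / (0.30 − 0.15)² = 112.66, so 113.

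113 / (1 − 0.20) = 141.25, so 142 per arm and 284 in total. This matches the stated figure. The design therefore budgets 5% one-sided for one comparison.

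**2. Error rate if either of two analyses may win at one-sided 0.05.**

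- Independent statistics: 1 − 0.95² = 9.75%. This is the upper case for statistics that are not negatively correlated.
- Correlated statistics: 1 − P(Z1 < 1.645 and Z2 < 1.645), bivariate normal. Assumed correlation 0.5 gives 8.8%, 0.7 gives 8.0%, 0.9 gives 6.8%.

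**3. Error rate under other rules.**

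- 36 months alone decides: 5%.
- Both must succeed: at most 5%.
- Either may win, but both tests are two-sided at 5%: the chance of a false result favouring the experimental arm is 2.5% at each time, so at most 2.5% + 2.5% = 5%.

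**4. What keeping two primary analyses would cost.** Splitting the level equally (one-sided 0.025 each) gives n = 0.41 × (1.960 + 0.842)² / 0.15² = 143.02, so 144 per arm. Then 144 / 0.80 = 180 per arm, 360 in total. With 284 enrolled and 142 × 0.80 = 113.6 per arm evaluable, the standard error is √(0.41/113.6) = 0.060, and power at each time is Φ(0.15/0.060 − 1.960), about 70%.

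**5. The 36-month clock.** The Abstract counts from randomization. Primary outcomes and {18a} count from the end of the 12-week intervention, so M36PI falls about 12 weeks later than the Abstract's time point.

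**The case against.** Much can be said against a harsher version of this point, and most of it stands.

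- **A reader might infer that no deciding time point exists.** The article does not support that. The Abstract names 36 months and Sample size {14} sets attrition there. The fault is that {20a} and {21b} do not agree with each other or consistently with the Abstract.
- **A reader might infer that each analysis is assigned the full 5%.** No sentence says so. The only level given for the primary outcome is one-sided 0.05 for one test; the 5% in {20b} stands under subgroup analyses. An either-may-win rule is neither stated nor excluded.
- **A reader might count five primary tests.** The five-visit sentence is a calculation schedule: Secondary outcomes uses practically the same sentence, and the Abstract analyses the follow-up with mixed models. An error rate for five tests would describe a procedure that the article does not plan.
- **The size is conditional.** The correlations are assumptions. Under {20c}, missing primary outcomes refer back to baseline. If that means baseline carried forward, women missing at both times count as not improved twice, which would raise the correlation and lower the inflation. The sidedness of the actual tests is not stated, and a chi-square test is ordinarily two-sided.
- **Multiplicity rules belong in the analysis plan, which is not shown.** That is fair for an alpha split or test order, and their absence here is not the finding. But a rule in that plan would not reconcile {20a} with {21b}, which are both in this text.
- **The single analysis in {21b} may only mean that there is no interim look.** That is possible given its heading, but it still leaves {20a} with two primary analyses against the Abstract's one time point.
- **The short-term comparison is a real objective.** Objectives {7} covers short-term and long-term change. This argues for keeping the comparison with a defined status, not for leaving its status open.

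**Conclusion.** The contradiction is established from the text alone: the Abstract gives one primary time point, {20a} gives two primary analyses, and {21b} gives one, against a sample size that reproduces exactly as one test at one-sided 0.05. The consequence for the error rate is conditional. If either analysis may win at one-sided 0.05, the false-positive chance is at most 9.75%, and about 7% to 9% at assumed correlations from 0.9 down to 0.5. If 36 months alone decides, if both must succeed, or if both tests are two-sided at 5% and only results favouring the experimental arm count, it stays within 5%. So the supportable statement is that the article does not show that 5% is kept, not that 5% is exceeded. The point should be corrected, preferably before long-term data accrue.

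**What to change.** - In Primary outcomes, {20a} and {21b}, name the 36-month comparison as the only confirmatory primary analysis, in line with the Abstract and Sample size {14}.
- State once, and use everywhere, whether the 36 months run from randomization or from the end of the 12-week intervention.
- Make the end-of-treatment comparison a key secondary that serves the short-term objective in {7}, tested confirmatorily only if the 36-month result is positive. This fixed order keeps the overall level at 5% without a split.
- Report the 6-, 12- and 24-month visits as estimates with confidence intervals.

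This is a change of wording, and the 284 of {14} stays as it is. The price is that the short-term result loses stand-alone confirmatory status. If the sponsor wants to keep that status, an equal split of the level is possible, but needs 360 women in total or leaves about 70% power at each time point with 284.

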### Objectives {7}

In this study, we aim to determine whether PFMT assisted by NMES and EMG biofeedback, in comparison to conventional PFMT, brings forth more satisfactory short-term and long-term changes anatomically and clinically among early postpartum POP patients and to compare the cost-effectiveness of both training programs.

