#### Secondary outcomes

The secondary outcome measures include:
The proportion of participants suffering from each symptom at the time of follow-upsThe average decreases in PFDI-20 score, PFIQ-7 score, IIQ7 score, and ED-5Q score and the average increase in PISQ-12 respectively from the baselineThe average grade of PFM strength at the time of follow-upsThe average EMG values in the pre-baseline, flick contraction, tonic contraction, endurance contraction, and post-baseline phases respectively at the time of follow-upsThe average value in the diameter of levator hiatus at the time of follow-ups

The secondary outcome measures are calculated with each follow-up (M0PI, M6PI, M12PI, M24PI, M36PI).

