### Data collection and management

#### Plans for assessment and collection of outcomes {18a}

Except for the past medical history that is only collected before and during the baseline visit, we will perform the rest of the items listed below in the baseline visit and follow-ups scheduled at and 6, 12, 24, and 36 months after the end of the intervention, to acquire primary and secondary outcome measures.

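### The mixed models for the questionnaire and EMG outcomes omit the end-of-treatment visit, although the protocol defines and collects those outcomes there

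*Protocol article*

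**What the plan says.** All references are to the protocol article.

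- **Objectives {7}.** The trial asks whether the instrumented programme "brings forth more satisfactory short-term and long-term changes anatomically and clinically".
- **Secondary outcomes.** "The secondary outcome measures are calculated with each follow-up (M0PI, M6PI, M12PI, M24PI, M36PI"). M0PI is the visit at the end of the intervention.
- **Plans for assessment and collection of outcomes {18a}.** Assessments take place at baseline and at "follow-ups scheduled at and 6, 12, 24, and 36 months after the end of the intervention". The wording is clumsy, but its natural reading includes a visit at the end of the intervention itself.
- **Statistical methods {20a}.** Multilevel mixed models are named for the continuous secondary outcomes (questionnaire scores, EMG values, VAS and a QALY/cost item) "for the repeated measurements at 6, 12, 24, and 36 months". No other analysis is named for these outcomes.
- **Statistical methods {20a}, other outcomes.** The primary outcome does have an end-of-treatment analysis: a chi-square test of "improvement of at least 1 level of POP-Q staging among experimental and control groups right after intervention", with adjusted logistic regression. The remaining secondary outcomes get "chi-square test and logistic regression for categorical outcomes (POP-Q staging, pelvic floor muscle strength"), with no visits clearly attached.
- **Plans to promote participant retention {18b}.** With consent, what was gathered from a woman before she withdrew will still be analysed.

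**The concern.** The outcome definition has five post-baseline visits and the model has four. The missing one, M0PI, closes the 12 weeks in which the arms are treated differently. After that, section 11a recommends the same weekly training frequency. M0PI is therefore the visit closest to the treatment contrast, and the clinical half of the short-term objective rests largely on the questionnaires measured there.

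Two things follow if section 20a is applied literally:

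1. Symptom and quality-of-life scores and EMG values have no named between-arm estimate at the end of treatment. An analyst who adds one departs from the stated visit list and chooses a method that was not fixed in advance, in a trial where participants know their allocation.
2. A woman seen at M0PI but not from month 6 onward contributes no post-baseline value to these models. This sits badly with section 18b.

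There is also a conditional risk. A likelihood-based mixed model handles drop-out that depends on observed results only when those results are in the model. If loss before month 6 depends on the M0PI result, leaving M0PI out removes that protection.

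**Working it through.** **1. Visit lists side by side**

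| Source | M0PI | 6 | 12 | 24 | 36 |
|---|---|---|---|---|---|
| Secondary outcomes (definition) | yes | yes | yes | yes | yes |
| Section 18a (collection) | yes | yes | yes | yes | yes |
| Section 20a (mixed models) | no | yes | yes | yes | yes |

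Five visits are defined and collected, four are modelled, and 5 − 4 = 1 is unused.

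**2. The base for counting women**

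Section 14 assumes 50% against 20% improved, a 15% margin, one-sided 0.05, 80% power and 20% attrition. With unpooled variance:

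n = (0.5×0.5 + 0.2×0.8) × (1.645 + 0.842)² / (0.30 − 0.15)² = 112.66, rounded up to 113 per arm.

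113 / (1 − 0.20) = 141.25, rounded up to 142 per arm, or 284 in total. This reproduces the stated figure, and nothing in this point changes it.

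**3. How many women could have M0PI as their only post-baseline value**

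Planned attrition is 0.20 × 284 = 56.8 women by 36 months. The document does not say when it occurs, so the share falling between M0PI and month 6 is an assumption:

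| Share of attrition in that window | Women | % of 284 |
|---|---|---|
| 0% | 0 | 0% |
| 25% | 14.2 | 5% |
| 50% | 28.4 | 10% |
| 75% | 42.6 | 15% |
| 100% | 56.8 | 20% |

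The Abstract and the Trial design and Sequence generation sections give 274 instead of 284. On that base the women number 13.7, 27.4, 41.1 and at most 54.8. The percentages are the same.

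**4. Effect on the 36-month contrast**

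This was checked by simulation on assumed inputs: 142 per arm, correlation 0.6 between visits, a true 36-month difference of 0.30 SD, about 10–11% lost between M0PI and month 6, 1,500 trials per scenario, and generalised least squares with known covariance. The slope is the fall in the log-odds of loss per SD of M0PI result.

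| Loss depends on M0PI result | Estimate with M0PI | Estimate without M0PI |
|---|---|---|
| Experimental arm only, slope 0.8 | 0.300 | 0.351 |
| Experimental arm only, slope 1.2 | 0.302 | 0.385 |
| Both arms alike, slope 0.8 | 0.301 (SE 0.1277) | 0.300 (SE 0.1304) |

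- One-sided loss: 0.351/0.30 = 1.17 and 0.385/0.30 = 1.28, so the estimate is 17% to 28% too large. In absolute terms this is 0.051 to 0.085 SD, less than one standard error (about 0.13).
- Equal dependence: no bias. The SE ratio is 0.1304/0.1277 = 1.02, about 2% larger.
- The Monte Carlo error of each mean is about 0.13/√1500 = 0.003, so the gap in the first two rows is not noise.

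**The case against.** **The list may describe a deliberate split.** The Abstract plans analyses "right after the intervention, and during the follow-up until 36 months, using the chi-square test and multilevel mixed models respectively". On that model, section 20a's list is the follow-up half, and a simple comparison at M0PI would sit beside it. The reading is coherent, but the Abstract states the split for the primary outcome. Section 20a then supplies the end-of-treatment test for the primary outcome and none for the continuous secondary outcomes.

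**The detail may be in the statistical analysis plan.** Section 20a defers to that plan, which is not shown, and a condensed article may leave model detail to it. Silence would be no finding. Here the article is not silent: it gives an explicit visit list that conflicts with its own outcome definition. The plan may already put this right, and that limits the severity.

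**Stronger readings that do not stand.**

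- A reader might infer that the short-term objective has no estimate at all. It does: POP-Q improvement is tested right after the intervention, and the categorical secondary outcomes are not confined to later visits.
- A reader might infer that early drop-outs are discarded as a rule. No sentence says so, and section 18b points the other way. The effect reaches only women whose sole post-baseline value is M0PI, and only in these models. Women lost before M0PI have no post-baseline value under either model.
- A reader might take 17–28% as the expected bias. It needs loss driven by response in one arm only, which nothing in the document supports.
- The document gives no basis for saying that the M0PI effect is the largest.

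**Conclusion.** The inconsistency stands. For the questionnaire and EMG outcomes, section 20a omits a visit that the protocol defines, schedules and needs for its short-term clinical objective. The certain cost is one of five visits unused and no named between-group estimate at M0PI for these outcomes.

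The rest depends on assumptions. The number of women adding no post-baseline data lies between 0 and about 57 of 284, or 14 to 43 if a quarter to three quarters of attrition falls before month 6. The article does not say whether baseline enters the models as a response or a covariate, so such women might still contribute baseline data. Bias in later contrasts arises only if loss after M0PI depends on the M0PI result differently by arm. With equal dependence, the cost in the simulated case is about 2% on the standard error.

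Severity is minor to moderate. The primary outcome, sample size and data collection are unaffected.

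**What to change.** In section 20a, and in the statistical analysis plan if it carries the same list, fit the mixed models for the questionnaire and EMG outcomes to M0PI, 6, 12, 24 and 36 months with treatment-by-visit terms. Report the M0PI contrast as the short-term effect and the 36-month contrast as the long-term effect.

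Do not extend this to the QALY and cost item in the same sentence. Those quantities accumulate over follow-up and belong to the economic analysis described in section 18a.

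The cost is a short change of wording. The M0PI data are already scheduled, no visit is added and the sample size does not change. The change brings the Objectives, the Secondary outcomes section and sections 18a, 18b and 20a into agreement on these outcomes.

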In the subsequent appointments, participants are asked to perform their current program, allowing the physiotherapist to adjust the program according to their progress. Once their PFM strength hits grade 3 in the Modified Oxford Scale, the Knack maneuver will be added. That is pre-contracting PFM against increases in intra-abdominal pressure, represented by coughs in practice. A total of 5 appointments, at the weeks 0, 1, 4, 8, and 12 respectively, will be offered for both groups over the 12-week intervention period.

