Past medical history. We collect the gestation and delivery information for a baseline from the hospital’s Electronic Medical Record System. The important prognostic covariates for the clinical effectiveness, including newborn weight, the length of first/second stage, infant head circumference, and maternal body mass index, will be recorded.Lifestyle information: the habits of smoking or drinking, and the frequency of moderate-intensity exercise, which is important covariates for the long-term effectiveness. POP-Q stage. Anatomical severity of pelvic organ descent is measured and staged in a POP-Q examination during each follow-up appointment.Prolapse symptoms. We document the presence of POP-related symptoms among participants in each follow-up appointment. Symptoms selected for inquiry are those frequently included in the validated questionnaires and reported by POP patients.Questionnaires. POP-related urinary, colorectal-anal, and pelvic symptoms are evaluated with Pelvic Floor Distress Inventory-Short Form 20 (PFDI-20) and sexual symptoms using Pelvic Organ Prolapse/Urinary Incontinence Sexual Questionnaire (PISQ-12). The impact of such symptoms on quality of life is assessed by the Pelvic floor Impact Questionnaire-Short Form 7 (PFIQ-7), Incontinence Impact Questionnaire-Short Form 7 (IIQ-7), and EuroQol Five Dimensions Questionnaire (EQ-5D). These questionnaires are instruments with evidence of validity, reliability, and responsiveness and have been translated into Chinese. Participants are referred to complete these questionnaires at the end of each follow-up appointment.PFM strength grade. PFM strength that reflects the muscle function is graded using the Modified Oxford Scale (MOS) in digital palpation during each follow-up appointment.PFM electromyography. Glazer Protocol consists of PFM EMG values in the pre-baseline, flick contraction, tonic contraction, endurance contraction, and post-baseline phases. Obtained in each follow-up, these EMG values indicate muscle activity from an electro-physiological perspective objectively.Pelvic ultrasonography. Three-dimensional ultrasonography is widely used to assess the morphology of the pelvic floor muscles and pelvic organs, including the diameter of levator hiatus and position of the bladder and rectum at rest and during maximum Valsalva.

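### PFM strength is defined as an average grade but assigned to a chi-square test and logistic regression, so no method named for it estimates or tests the stated outcome

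*Protocol article*

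**What the plan says.** Three parts of the protocol article bear on this outcome.

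- **Definition.** The Secondary outcomes section lists the mean grade of PFM strength among its measures and adds: "The secondary outcome measures are calculated with each follow-up (M0PI, M6PI, M12PI, M24PI, M36PI". The quantity of interest is therefore an average, at five visits.
- **Measurement.** Section {18a} states: "PFM strength that reflects the muscle function is graded using the Modified Oxford Scale (MOS) in digital palpation during each follow-up appointment". Section {11a} treats the grades as ordered, because reaching a given grade triggers a change in the programme: "Once their PFM strength hits grade 3 in the Modified Oxford Scale, the Knack maneuver will be added".
- **Analysis.** Section {20a} assigns "the multilevel mixed models for continuous outcomes (PFDI-20, PFIQ-7, PISQ-12, and ICIQ SF-7 scale scores, pelvic floor muscle electromyography values" and some further measures to mixed models for repeated measurements. PFM strength is not in that list. It appears in the next clause: "chi-square test and logistic regression for categorical outcomes (POP-Q staging, pelvic floor muscle strength". No trend test, ordinal model or cut-point is named.

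**The concern.** The definition calls for a difference in mean grade between arms, but the analysis section files the same variable under categorical outcomes. A Pearson chi-square test on a grade-by-arm table asks whether the two distributions differ in any way. It gives no mean difference, treats a move from grade 2 to 3 like a move from grade 2 to 5, and makes no use of the repeated visits. Logistic regression does not return a mean difference either.

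Two things are at stake. A significant chi-square result need not mean that strength has shifted. And when strength does shift in one direction, the test spreads its power over patterns that nobody expects. An analysis plan drafted to follow section {20a} would carry the mismatch forward.

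**Working it through.** **1. The plan's own figure.** The protocol gives no power for PFM strength, so the sample size section serves only to fix the number evaluable. Inputs from section {14}: "we estimate the proportion of participants with improved POP-Q stage to be 50% in the experimental group and 20% in the control group"; "we set the testing margin as 15% which indicates the significant clinical effectiveness"; one-sided 0.05; 80% power; 20% attrition.

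n per arm = (1.645 + 0.842)² × (0.5×0.5 + 0.2×0.8) / (0.30 − 0.15)² = 112.7, so 113. With attrition, 113 / 0.8 = 141.25, so 142 per arm and 284 in total. This reproduces the stated figure. Section {16a} instead gives a sequence of 274, which leaves 137 × 0.8 = 109.6, about 109 evaluable per arm. Both 113 and 109 are used below.

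**2. Does a chi-square over grades test the average?** Take two assumed six-grade distributions with the same mean (2.5) and 113 per arm. In simulation the chi-square test rejected in over 99% of trials and the t-test on mean grade in about 5%. The example is deliberately extreme. It shows only that the two tests address different hypotheses.

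**3. Power for a one-directional shift, general form.** Assume two-sided 5%; the article states a 5% level only in its subgroup section. A 1-df test with 80% power has noncentrality (1.96 + 0.842)² = 7.85. With the same signal, an unordered chi-square over k occupied grades has k − 1 degrees of freedom:

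| Occupied grades | df | Power |
|---|---|---|
| 3 | 2 | 0.709 |
| 4 | 3 | 0.645 |
| 5 | 4 | 0.595 |
| 6 | 5 | 0.555 |

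The loss runs from 80 − 70.9 = 9.1 points to 80 − 55.5 = 24.5 points.

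**4. Simulation with six grades.** Assumed: three control distributions (symmetric, narrow, flat), a proportional-odds shift, 109 or 113 per arm, and 3,000 trials per setting. Ranges are across distributions and sample sizes.

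| Odds ratio | Chi-square | Rank test or t-test on mean grade |
|---|---|---|
| 1.5 | 19–22% | 35–40% |
| 1.8 | 41–44% | 62–70% |
| 2.0 | 55–58% | 77–83% |
| 2.5 | 84–86% | 95–97% |

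An odds ratio of 2.0 corresponds here to a mean difference of 0.32 to 0.55 grade. A binary cut at grade 3 or 4 gives 61–72% at that odds ratio, between the two columns. The t-test on the mean performs about as well as the rank test, so keeping the average as the outcome costs almost nothing in power.

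**The case against.** The strongest reply is that section {20a} names logistic regression beside the chi-square test and does not call it binary there; that word qualifies only the primary-outcome model. A proportional-odds model is a logistic regression. It would use the order and recover most of the power. The form of the model, any cut-point and the handling of repeated visits are details that an article may leave to the analysis plan. This stands, and it limits the point. A reader might infer that the protocol prescribes an unordered test and a dichotomised model. The word unordered does not appear. It is the plain reading of a chi-square test with no trend test named, but it remains a reading.

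The reply does not remove the mismatch. Whatever form the logistic model takes, it yields an odds ratio and not a mean grade. For the same reason, a proportional-odds model alone does not satisfy the definition unless the outcome is reworded.

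A second reply concerns size. The article gives no number of grades, distribution, expected effect or power target for PFM strength, and 113 is the evaluable number for the primary outcome at 36 months; earlier visits may have more women. This also stands. A reader might infer that the trial will probably miss a real change in strength. The figures do not support that: at an odds ratio of 2.0 the chi-square test still detects the shift in more than half of trials, and at 2.5 in 84–86%.

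A reader might also infer that strength is the main mechanism of the treatment. The Background lists it with endurance, coordination, timing, tone and hypertrophy, and nowhere ranks it first.

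**Conclusion.** The point holds as an inconsistency between two sections. PFM strength is defined as an average of an ordered grade at five visits, and no method named for it tests or estimates that average. This part needs no assumption.

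The power cost does rest on assumptions. Relative to a 1-df test with 80% power, it is about 9 points with 3 occupied grades and about 25 with 6. With six assumed grades, the gap is about 15 to 27 points for odds ratios of 1.5 to 2.0 and about 10 to 13 points at 2.5.

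This is one of several secondary outcomes. The primary comparison and the sample size calculation do not depend on it.

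**What to change.** Reconcile the Secondary outcomes section with section {20a}. Drop the chi-square test for PFM strength and adopt one of two routes:

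1. **Keep the average.** Add PFM strength grade to the multilevel mixed models already planned for the repeated scores, adjusted for baseline grade, and report the mean difference by visit. This is the smaller change. Section {20a} lists only 6, 12, 24 and 36 months for those models, so say how the visit right after the intervention (M0PI) enters.
2. **Redefine the outcome** as the distribution of grades. Specify the logistic regression as a proportional-odds mixed model adjusted for baseline grade, report the common odds ratio, and give mean grade by arm as description.

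The cost is a few lines in the protocol and analysis plan and slightly more modelling. No new data or visits are needed.
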